### Statistical analysis

2.11

The Graph Pad InStat 3.10 software will be used for statistical analysis, with a 5% level of significance. All data will be first checked for normality test. Continuous variables having normal distribution will be considered as mean ± standard deviation and will be compared using the t-test. Non-normally distributed data will be analyzed using the Mann-Whitney test. All the categorical variables, expressed in numbers and percentages, will be compared using the Fisher exact test.^[20]^

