### Sample size

2.10

The trial sample size is represented by 100 subjects with anatomically significant coronary artery disease depicted by CCTA examination. The lot size estimation was done using the StatMate 2.0 software. A percent of 60% event-free study population was estimated for sample size calculation%, and a sample size of 50 subjects in each group is associated with a power of 90% for detection of an increase of 0.29 in MACE-free rates proportion, with a significance level (alpha) of 0.05 (two-tailed). Consequently, the study lot population including the 2 study groups of 50 patients each, was set at 100 patients.

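### Section 2.11 lets a normality test choose between the t-test and Mann-Whitney and does not address unequal variances, so the error rate can depart from 5% in either direction in unequal MACE groups

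*Protocol article*

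**What the plan says.** Section 2.11 (Statistical analysis) of the protocol article sets a two-step rule for continuous variables, "with a 5% level of significance". The first step is the check: "All data will be first checked for normality test". The second depends on its result. For variables that pass, "Continuous variables having normal distribution will be considered as mean ± standard deviation and will be compared using the t-test". For the rest, "Non-normally distributed data will be analyzed using the Mann-Whitney test". Categorical variables go to the Fisher exact test.

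The section does not mention variances, does not say which form of t-test is meant, and does not name the groups to be compared.

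Two other sections matter here. Section 2.8 (Outcomes) makes the primary outcome the 1-year rate of ischaemia-related MACE, related to stenosis degree and to ischaemia or viability. Section 2.10 (Sample size) gives the planning rates: "A percent of 60% event-free study population was estimated for sample size calculation", with two groups of 50 and 90% power "for detection of an increase of 0.29 in MACE-free rates proportion".

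**The concern.** The rule has two weaknesses.

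First, a preliminary p-value decides what is estimated. One biomarker may be summarised as a difference in means and the next by a rank comparison, for no reason other than how its normality test came out in this sample. This does not depend on group sizes or variances.

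Second, the rule tests the less important assumption. When two groups differ in size, the equal-variance t-test is sensitive to unequal SDs, and a normality test cannot detect that. The two enrolment groups are equal in size, but a comparison of patients with and without MACE would not be. For continuous predictors of MACE, the nominal 5% could then be too high or too low, and a reader of the results could not tell which.

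**Working it through.** **1. The plan's own figure.** MACE-free proportions of 0.60 and 0.60 + 0.29 = 0.89, 50 per group, two-sided alpha 0.05. Exact enumeration of the Fisher test gives 90.2% power, so the stated 90% is reproduced. This calculation concerns proportions and does not involve the t-test rule.

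**2. Group sizes implied by the planning rates.**
- 60% event-free in all 100 patients: 40 with MACE, 60 without.
- Mean of the two planning rates: (0.60 + 0.89)/2 = 0.745 event-free, or 25.5 events per 100, so about 25:75.
- The two enrolment groups: 50:50.

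**3. Why unequal SDs matter.** Let the smaller group have size n1 and SD s, and the larger have size n2 and SD 1. The true variance of the difference in means is s²/n1 + 1/n2. The equal-variance t-test estimates it as sp²(1/n1 + 1/n2), where sp² = [(n1−1)s² + (n2−1)]/(n1+n2−2). With k² = true/estimated, the error rate is approximately 2[1 − Φ(1.96/k)].

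- 40:60, s = 1.5: true = 2.25/40 + 1/60 = 0.0729. sp² = (39×2.25 + 59)/98 = 1.497, so estimated = 1.497 × 0.04167 = 0.0624. k = 1.081, 1.96/k = 1.813, error about 7.0%.
- 25:75, s = 2: true = 4/25 + 1/75 = 0.1733. sp² = (24×4 + 74)/98 = 1.735, so estimated = 1.735 × 0.05333 = 0.0925. k = 1.369, 1.96/k = 1.432, error about 15.2%.
- 25:75, s = 0.5: true = 0.25/25 + 1/75 = 0.0233. sp² = (24×0.25 + 74)/98 = 0.816, so estimated = 0.0435. k = 0.732, 1.96/k = 2.677, error about 0.7%.
- 50:50: true and estimated are equal for any s, so the error is about 5%.

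**4. The full two-step rule, by simulation.** 20,000 replicates per setting, normal data with equal means. Shapiro-Wilk at 0.05 was run in each group; if both passed, the equal-variance t-test was used, otherwise Mann-Whitney. The normality test and the SD ratios are assumptions, because the article gives neither.

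| Split | SD ratio 2 | 1.5 | 1 | 0.67 | 0.5 |
|---|---|---|---|---|---|
| 50:50 | 5.6% | 5.3% | 5.2% | 5.2% | 5.1% |
| 40:60 | 8.5% | 7.2% | 5.0% | 3.5% | 3.1% |
| 25:75 | 14.8% | 10.1% | 5.2% | 1.8% | 0.9% |

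The SD ratio is smaller group to larger group (first to second at 50:50).

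**5. What the pre-test contributes.** The rule's error is within about 0.5 points of the t-test used without any gate (at 25:75 and ratio 2, 14.8% against 14.9%). The normality check neither causes the problem nor guards against it. Mann-Whitney alone drifts in the same directions: at 25:75, 7.4-9.8% for ratios 1.5-2 and 1.9-2.8% for ratios 0.5-0.67.

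**6. The alternative.** Welch's t-test used throughout stays at 4.4-5.4% over all these settings and also at a 15:85 split. On raw, strongly skewed data it is less reliable: about 10% at 11:89 with lognormal values. On the log scale it gave 4.6-5.1% in lognormal runs.

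**The case against.** The strongest reply is that section 2.11 names no MACE versus no-MACE comparison of continuous variables. The only groups the article defines are the two enrolment groups of 50, and there the error is at most 5.6%. The section also says only that a t-test will be used. If that means Welch's form, most of the departure disappears, and the form may be set out in a fuller plan that is not shown. The article gives no SDs, so nothing shows that variances differ. The gate barely changes the error rate, so deleting it alone would not cure the problem. Choosing between means and ranks by a normality test is also a common convention.

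Most of this stands and limits the point. A reader might infer that false-positive rates exceed 5% under this plan. The documents do not support that. Inflation needs a MACE comparison, an equal-variance t-test, unequal variances, and the larger variance in the smaller group. With the reverse pairing the test is conservative and loses power.

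Three things remain. The pre-test is written into the article, so it is not an omission. With only t, Mann-Whitney and Fisher tests listed, relating a continuous measure to MACE leads naturally to comparing patients with and without events. And reading the t-test as Welch's repairs only one branch, because Mann-Whitney is affected too.

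**Conclusion.** The point holds as a minor one. As written, the rule leaves the quantity compared to be settled by the data and takes no account of unequal variances. At the splits implied by the planning rates, type I error for continuous comparisons can run from about 1-4% to about 7-15%, according to which group has the larger SD. This rests on three assumptions: that the comparison is between patients with and without MACE, that the t-test is the equal-variance form, and that SDs differ by a factor of 1.5 to 2. Without unequal SDs, or in the planned 50:50 groups, the rate stays near 5%. The Fisher comparison of MACE proportions and the stated 90% power are not touched.

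**What to change.** Remove the normality pre-test from section 2.11 and name the test for each variable in advance:

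- Continuous CT and echocardiographic measurements: Welch's t-test.
- hs-CRP, IL-6, MMP-9 and NT-proBNP: Welch's t-test on the log scale, reported as a ratio of geometric means with a 95% CI.
- Ordinal scores (plaque vulnerability, Duke Jeopardy): a pre-specified rank test. Welch's test for every CT-derived quantity would be too broad.

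This takes a few sentences. When variances are equal, Welch's test loses about 1 point of power or less. The rank test for the scores keeps some sensitivity to unequal spread, which is acceptable for a small number of ordinal measures if the choice is made beforehand.

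### Optional improvement: for 2x2 comparisons, section 2.11 could name the Boschloo exact test instead of the valid but conservative Fisher exact test, with the same 5% error bound and somewhat more power

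*Protocol article*

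**What the plan says.** Section 2.11 (Statistical analysis) names a software package that "will be used for statistical analysis, with a 5% level of significance". It then assigns a single test to all categorical data: "All the categorical variables, expressed in numbers and percentages, will be compared using the Fisher exact test".

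Section 2.10 (Sample size) gives the design inputs. The reference rate is stated as "A percent of 60% event-free study population was estimated for sample size calculation". The target is "detection of an increase of 0.29 in MACE-free rates proportion", "with a significance level (alpha) of 0.05 (two-tailed"), and "a sample size of 50 subjects in each group is associated with a power of 90" per cent. The section does not say which test that calculation assumed. Section 2.8 makes the 1-year MACE rate the primary outcome, so the test named in 2.11 governs the comparison for which the study was sized.

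**The concern.** With two groups of 50 a 2x2 table can produce only a limited set of p-values. Fisher's test conditions on the total number of events, which makes that set coarser still. It rejects only when the p-value is at or below 0.05, so its long-run false-positive rate lies below 5%, and well below when events are few. A test that uses more of the allowed 5% without exceeding it would find true differences more often in the same patients. In a study of 100 patients with a binary main endpoint, that is worth having if it costs nothing in error control.

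**Working it through.** **Inputs.** From section 2.10: 50 per group, two-sided alpha 0.05, MACE-free rate 0.60 against 0.60 + 0.29 = 0.89, stated power 90%. From section 2.11: Fisher exact test, 5% level. All other event rates and group splits below are assumptions, used to show the range.

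**Method.** List all 51 x 51 = 2,601 possible outcomes (i, j) of MACE-free counts in the two groups and compute the two-sided Fisher p-value of each. For a rejection region R:

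- power(p1, p2) = sum over (i, j) in R of Bin(i; 50, p1) x Bin(j; 50, p2)
- true size(p) = power(p, p), maximised over p from 0.001 to 0.999

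For Fisher, R is every table with p-value at or below 0.05.

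**Step 1: the plan's own figure.** Fisher power at 0.60 versus 0.89 is 90.2%, which reproduces the stated 90%. With 49 per group it is 89.4%, just short of 90%. Section 2.10 therefore fits the test named in 2.11.

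**Step 2: Fisher's true size at 50/50.**

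| Common event rate | True size |
|---|---|
| 5% | 0.7% |
| 10% | 1.8% |
| 15% | 2.4% |
| 20% | 2.8% |
| 25% | 3.0% |
| 50% (maximum) | 3.5% |

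**Step 3: other splits of 100 patients.** Fisher's maximum size is 4.6% at 49/51, 4.4% at 48/52, 4.5% at 47/53, 4.4% at 45/55, 4.0% at 40/60 and 4.3% at 30/70. The 3.5% maximum belongs to exact equality.

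**Step 4: the Boschloo test.** Order tables by the Fisher p-value and take the largest cut-off c for which the maximum true size is at most 5%. At 50/50, c = 0.0693 with maximum size 4.87%; the next attainable value, 0.0704, gives 5.06% and fails. Because c is above 0.05, every table that Fisher rejects is rejected here too. The true size is 3.2% at a 10% event rate and 4.0% at 20%.

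**Step 5: power at 50/50.**

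| MACE-free rates | Fisher | Boschloo | Gain (points) |
|---|---|---|---|
| 0.60 vs 0.89 (design) | 90.2% | 92.2% | 2.0 |
| 0.70 vs 0.90 (assumed) | 64.0% | 69.6% | 5.6 |
| 0.80 vs 0.95 (assumed) | 50.8% | 58.3% | 7.5 |
| 0.85 vs 0.98 (assumed) | 51.0% | 63.1% | 12.1 |

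**Step 6: does the gain survive other splits?** It does, but unevenly. For 0.85 versus 0.98 (first group size with the first rate), power goes from 64.2% to 72.3% at 49/51, from 68.3% to 69.1% at 47/53 and from 64.9% to 65.9% at 45/55; at 51/49 the gain is about 12 points. At 30/70, 0.60 versus 0.89 goes from 86.4% to 90.5%.

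**Step 7: the common alternatives at 50/50, design point.** Pearson chi-square has power 93.5%, but its true size reaches 5.7%, above the bound. Mid-p Fisher has power 91.3% and maximum size 3.7%; at 49/51 its maximum is 5.04%, so it does not guarantee 5%. Boschloo keeps the bound by construction.

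**The case against.** The strongest reply is that nothing here is wrong. Fisher's test is a standard, valid choice, no sentence in the article promises an attained error rate equal to 5%, and the planned sample size already pays for the test's conservatism. All of this stands.

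A reader might infer three stronger things that the documents do not support:

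- **That the stated 5% level is not used.** It is: 5% is the cut-off for the p-value. A discrete exact test whose true size lies below its cut-off does not contradict section 2.11.
- **That the study falls short of its power.** At the inputs of section 2.10 Fisher gives 90.2%, as stated. The comparison is with a better test, not with the plan.
- **That 3.5% is a general ceiling.** It needs exactly 50 and 50 analysed. The groups are defined by clinical status, not randomised, and one patient's imbalance raises the maximum to 4.6%. Section 2.8 also relates MACE to stenosis, ischemia and viability, and no 50/50 split is set for those.

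It is also fair to object that the larger gains rest on event rates absent from the documents, which assume 60% event-free, and that they vary with the split. That stands too, so only the 2-point gain at the design point can be claimed from the plan's own figures.

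The objection that Fisher's conservatism buys a guaranteed error bound holds against Pearson chi-square. It does not hold against Boschloo, which gives the same guarantee.

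**Conclusion.** This is a cheap improvement and not an error. Fisher's test is valid, applies the 5% level and meets the stated 90%. A uniformly more powerful test with the same 5% guarantee exists for 2x2 tables. The gain is about 2 power points at the design point (90.2% to 92.2%). Under the assumed lower event rates it is about 6 to 12 points at exactly 50/50, and in other splits it ranges from under 1 to about 12 points. These figures rest on two independent binomial samples, two-sided testing at 0.05 and complete outcome data; the lower event rates are assumptions. Leaving section 2.11 as it stands would be defensible.

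**What to change.** In section 2.11, name the Boschloo unconditional exact test (two-sided, 5%) for 2x2 comparisons, including MACE-free yes/no between the two groups, with a matching exact confidence interval for the difference in proportions. Keep the Fisher exact test for larger tables. Section 2.10 needs no change in sample size; it may note that power for the same inputs becomes about 92%.

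The cost is one sentence and no patients. These tables may have to be run in freely available software other than the named package, if that package does not offer the test. The choice must be fixed before any outcome data are seen, because a later switch to a more powerful test would not be credible.

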## Discussion

3

This paper presents the protocol of a prospective, single-center clinical study which aims to determine the effectiveness of a new imaging tool based on fusion imaging in the complex assessment of coronary lesions. The present study was designed to validate a new and robust imaging method, superior to the conventional ones, used to determine the functional impact of coronary lesions on the myocardial tissue.

The impact of coronary artery stenosis on the myocardial contraction was addressed by multiple studies. It is well known that interventional assessment of coronary physiology during invasive coronary angiography may indicate the presence or absence of myocardial ischemia in the territory irrigated by the stenotic artery. Fractional flow reserve is an invasive procedure which may assess the impact of the coronary stenosis on the myocardial ischemia with an accuracy of 90%.^[21]^ The multicenter FAME study investigated the role of FFR-guided PCI compared to angiography-guided PCI, on clinical outcomes in patients undergoing coronary revascularization. After 5 years of follow up, MACE occurred more frequently in the angiographic-guided PCI, however with no statistical significance (31% vs 28%; RR-0.91, 95% CI, p-0.31).^[22]^ A recent analysis of the SCAAR registry (Swedish Angiography and Angioplasty Registry) that involved all patients treated with PCI in Sweden between 2005 to 2016, indicated that patients who underwent FFR-guided PCI had a 19% reduction in mortality after 5 years compared to those patients who performed angiography-guided PCI (*P* < .0001).^[23]^

However, these are invasive techniques that imply the risk associated with any interventional procedure. Therefore, identification of non-invasive imaging tools may help to better discriminate the lesions requiring treatment, which is particularly important especially in the case of multivessel disease. In a recent article, Savic et al found that multi-vessel disease remains an independent predictor for 6-year cardiovascular mortality (HR 1.55, 95% CI 1.11–2.06, *P* = .041), with a six-year cardiovascular mortality significantly higher than in patients with single-vessel disease (10.4% vs 4.6%, *P* < .001).^[24]^

Location of coronary lesions may also play a significant role on the clinical outcomes, since it has been demonstrated that an increased shear stress at the level of coronary bifurcations may accelerate the plaque vulnerabilisation process,^[25]^ while location in the proximal left anterior descendant artery is association with an increased risk of cardiac arrest.^[26]^

The FUSE-HEART study seeks to validate the usefulness and efficacy of fusion imaging by integrating anatomic information provided by CCTA with functional information provided by the same techniques, in order to identify the impact of a stenosis on subjacent myocardial contractility. In the case of multivessel disease, this fusion imaging may help to understand the complex interaction between different myocardial areas irrigated by stenotic arteries of the same heart.

At the same time, the impact of a coronary lesion results not only from its anatomical severity, but also from its composition. It has been demonstrated that vulnerable plaques triggering an acute cardiac event exhibit a different CCTA phenotype than plaques that remain un-ruptured. In a recent study by Licu et al, the most relevant vulnerability markers associated with an acute coronary event were presence of low attenuation within the plaque (*P* < .0001) and positive remodeling (*P* < .0001), while low attenuation plaques was the strongest independent predictor of acute myocardial infarction at 6 months (OR 8.18 [1.23–95.08], *P* = .04).^[27]^ Systemic inflammation may play also a significant role in the complex process of plaque vulnerabilisation and also in the evolution in the period of time post myocardial infarction^.^^[28,29]^ Therefore, the FUSE-Heart study will include a biomarker sub-study in order to investigate the association between systemic vulnerability and local factors that favor plaque vulnerabilisation, as well as the reflection of this association on plaque vulnerabilisation at a local level.

## Conclusions

4

FUSE-HEART will be the first study based on fusion imaging that will investigate the impact of a coronary lesion on myocardial contractility, aiming to validate fusion-imaging as an effective alternative tool in the CCTA assessment of coronary circulation.
